## Discussion

Pilot studies are essential for improving the quality and efficiency of the major study (49). Thus, the success of this pilot program could help set the foundation for sustained oral health education training for primary health care workers, invariably creating a pool of qualified peer trainers for PHC workers, PHC patients, their families, and the general population. Studies have shown how misinformation, myths and cultural beliefs among individuals and community stakeholders negatively impact oral health attitudes and care-seeking behaviors in developing countries (50–54). Promoting approaches where qualified care professionals provide adequate and accurate oral health information may thus influence positive oral health practices, leading to improved oral health and overall health. The scope of the current project will encompass most of the essential components of primary oral care recommended by the WHO by leveraging the strategic positioning of the PHC system and its link with individuals, communities, and the health care system. These recommendations include “*age-friendly primary health care for oral health, maternal and child oral health care, health communication/oral health education, disease prevention methods, early detection, pain control - emergency care for oral health, continuity of oral healthcare, supportive referral systems and priority to those people most in need*” (7). The strength of the QED approach lies in its simplicity regarding data collection, ease of implementation and associated low cost (55). However, there are some limitations to this study design. Due to non-randomization of study participants, other factors related to the outcome of interest beyond the control of the researchers could potentially influence study results (56). Secondly, it is impossible to determine causality because quasi-experimental research is not an actual experiment; thus, only associations between interventions and outcomes can be made (43). Furthermore, because the treatment and control groups are nonequivalent (group assignment is by non-random selection), selection bias may exist. The presence of a nonequivalent no-treatment control in this study reduces issues such as threats to internal validity (i.e., observing the same participants over time). This is due to the assumption that the presence of similarity between the treatment and the control groups at baseline reduces the likelihood of having significant confounder differences between both groups (55, 57, 58).

In this study, we will ensure that a consistent approach is taken to select participants within and across study sites, administer evaluation surveys and follow-up (59). Additionally, we will conduct a pre-intervention assessment (allowing for the baseline comparison of the treatment and control group), an immediate post-intervention assessment, and 3 months following the training to allow for consideration of learning or attitude decay (43). Before use, the pre and post-tests will be validated for accuracy in measuring the outcomes of interest in the study. Also, tests will be scored consistently by a non-biased grader blinded to the participants and not part of the team that designed or conducted the oral health training (43). Regarding the establishment of causality, given that the intervention- (oral health education) comes before the assessment of the outcome, associations identified in QEDs meet an essential causality requirement (60).

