**Methods:**

This study will utilize a quasi-experimental design (pre-and post with a non-equivalent control group) to assess the impact of a five-day pilot oral health education program on the knowledge and referral practices of Nurses and Community Health Workers in primary health care centers in three states in Nigeria-(Lagos, Oyo, and Kano). The training modules were developed based on the six iterative steps described in the intervention mapping framework – needs assessment, highlighting program objectives and outcomes, selection of theory and mode of intervention, designing program based on theory, designing implementation plans, and developing an evaluation plan. Only the intervention group will participate in the full educational training sessions but both groups will complete the pre-and post-intervention questionnaires.

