### Research question

Does the introduction of oral health education modules by designated trainers improve the oral health knowledge, attitude, and referral practices regarding oral conditions in PHC Nurses and CHWs?

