#### Null hypothesis

No measurable difference will be observed in the post-intervention knowledge scores and referral practices as it relates to oral health between participants with access to the 5-day training workshop vs. the control group.

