### Intervention and control

The intervention and control groups will consist of participants selected by a non-random process but with comparable characteristics. Across the three study sites, a total of 60 PHC workers (20 Nurses and CHWs at each site) will be assigned to the intervention group, and a corresponding number of participants will constitute the control group. Participants in the control group will receive a one-off conventional oral health education session consisting of a lecture on oral health, tooth brushing, and diet and oral hygiene demonstration using dental models. The intervention group will be exposed to the week-long pilot training on oral health education delivered by designated trainers (see Table 2). They will also participate in group activities such as oral exams and activity sheets. Each module is expected to last for approximately 4 h. Participants in the intervention group (those who will be trained) will be compared to the control group at each study site. Before the training begins, each participant will be administered a pre-intervention questionnaire to evaluate their oral health knowledge at baseline. The assessment will be repeated immediately after training and after 3 months. These evaluations not only serve as a means of monitoring training impact but also allow participants to observe how they improve throughout the training.

**Table 2 tab2:** Program and module delivery for the five-day training.

Day	Module
Day 1	Pre-intervention test Introduction to oral health
Day 2	Introduction to oral diseases and conditions
Day 3	Techniques in oral health promotion and oral disease prevention
Day 4	School and community-based oral health promotion
Day 5	MCOH Post-intervention test Facilitator assessment of participants capability to provide oral health education.

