### Program assessment/evaluation

The assessment of the study outcome will be performed using a quantitative and a qualitative approach. Quantitative assessment will be conducted using questionnaires administered by the designated trainers, and the data will be fed into the Qualtrics software for data management. Before the training commences, all participants will take the pre-intervention test that measures their initial knowledge of oral health. The questions will be co-developed by Dental Public Health (DPH) consultants and educators on the research team based on available evidence and will be assessed for face and content validity before deployment. The questionnaire will also be pre-tested among participants who would not be involved in the study. The control group will be immediately provided with the post-intervention evaluation after the one-day lecture. After the training, participants in the training group will be assessed using the post-test. The pre and post-test scores will be compared for participants in the treatment and control groups. Participant’s capability to screen and detect oral diseases will be assessed post-intervention using picture tests.

After 3 months, a follow-up evaluation will be conducted. The number of logged referrals from the PHCs to the dental centers for oral health conditions will also be assessed for 3 months post-training based on the information logged by these providers (see Logic Model-Table 1). In addition, 5% of patients who were referred to dental centers as entered in the logbooks will be contacted via phone calls to verify their final visit to the dental centers.

The qualitative assessment to assess the impact of the training, points of improvement and the practicability of incorporation of oral health promotion activities into maternal and child health visits will be conducted with select participants in the intervention group at the 3-month evaluation using Deliberative Focus group discussions. This approach to evaluation serves to enhance program feedback through participants’ experiences and opinions. Refresher training will be conducted accordingly in month three if necessary. Data collection will be from February to May 2024.

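### The Discussion calls the comparison group a no-treatment control, but controls receive an oral health lecture and demonstration, so the knowledge contrast is five-day training beyond a single lecture

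*Protocol article*

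**What the plan says.** In the Discussion, among the strengths and limits of the design, the article states: "The presence of a nonequivalent no-treatment control in this study reduces issues such as threats to internal validity". The next sentence bases this on an assumption that the two groups are similar at baseline.

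The Methods, under Intervention and control, state: "Participants in the control group will receive a one-off conventional oral health education session consisting of a lecture on oral health, tooth brushing, and diet"; the sentence goes on to a hygiene demonstration on dental models. Under Program assessment/evaluation the timing is given: "The control group will be immediately provided with the post-intervention evaluation after the one-day lecture". For the other group, "The intervention group will be exposed to the week-long pilot training on oral health education delivered by designated trainers".

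Elsewhere the comparator is left unnamed. The abstract says: "Only the intervention group will participate in the full educational training sessions but both groups will complete the pre-and post-intervention questionnaires", and does not mention the lecture. The null hypothesis sets the contrast as "between participants with access to the 5-day training workshop vs. the control group", and the alternate hypothesis is framed in the same way. The research question names no comparator: "Does the introduction of oral health education modules by designated trainers improve the oral health knowledge".

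**The concern.** The Discussion is the only place that names the type of control, and the type it names is not the one the Methods deliver. This affects interpretation because the lecture teaches the subject of the test. Oral health knowledge is scored before and after in both groups, and controls are scored immediately after being taught. A reader who accepts the label would take the change in controls as background change (retesting and passage of time) and would take the between-group difference as the effect of training against no education. Neither reading fits the design. What is at stake is the conclusion on knowledge: a small or null difference could be reported as no benefit of training when both groups had learned.

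**Working it through.** **1. The texts side by side**

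| Place in the article | What it says of the controls |
|---|---|
| Discussion | No treatment |
| Methods, Intervention and control | One session: lecture on oral health, tooth brushing and diet, with a hygiene demonstration |
| Methods, Program assessment/evaluation | Post-test directly after the one-day lecture |
| Abstract, Methods | Not in the full sessions; lecture not mentioned |
| Hypotheses | Control group, content not stated |

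The first row cannot stand beside the second and third. The last two rows fit either reading.

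**2. What the knowledge contrast estimates**

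Let *T* be the mean gain from the five-day training and *L* the mean gain from the lecture, each against no education. Let *b* be the background change from retesting and time, taken as equal in the two groups.

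- Change in the intervention group: *T* + *b*
- Change in the control group: *L* + *b*
- Difference: (*T* + *b*) − (*L* + *b*) = *T* − *L*

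Under a no-treatment control, *L* would be 0, the control change would be *b* and the difference would be *T*. With the lecture, the control change is *L* + *b* and the difference is *T* − *L*. The shared background still cancels, so the value of a concurrent control does not depend on *L* being 0.

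**3. The plan's own figure**

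The sample size is 3 sites × (20 + 20) = 120, or 60 per group, as stated. It is a feasibility figure with no power calculation, and the point does not depend on it.

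**4. Illustration, with assumed effects**

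The article gives no effect size or SD. Assume 60 per group, two-sided α of 0.05 and no clustering. The difference detectable with 80% power is (1.960 + 0.842) × √(2/60) = 0.51 SD. Approximate power for a true difference *d* is Φ(*d*√(60/2) − 1.960), with *d* = *T* − *L*:

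| Lecture gain as a share of *T* | Power if *T* = 0.5 SD | Power if *T* = 0.8 SD |
|---|---|---|
| 0% | 78% | 99% |
| 25% | 54% | 91% |
| 50% | 28% | 59% |
| 75% | 10% | 19% |

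For example, *T* = 0.5 and *L* = 0.25 give *d* = 0.25, and Φ(0.25 × 5.477 − 1.960) = Φ(−0.59) = 0.28. The table shows only that a non-significant difference can coexist with real learning in both groups. It does not predict this trial's result.

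**The case against.** The strongest reply is that this is one wrong label in the Discussion, while the operative Methods text is clear and consistent. Much of that stands.

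- **The validity argument.** A reader might infer that the internal-validity claim collapses once the control is seen to be taught. The documents do not support that. The article rests the claim on baseline similarity, which applies equally to a lecture control, and a concurrent group still absorbs background change common to both groups.
- **The hypotheses.** They refer only to the control group, which the Methods define. They are incomplete rather than wrong. Reading the research question as modules against nothing goes beyond its words.
- **The analysis.** Pre and post scores are compared in both groups, and Data analyses plans within-group as well as between-group tests, so a gain among controls would be visible. This makes the misreading less likely. It does not prevent it, because a reader who trusts the label could put that gain down to retesting.
- **The later study.** A reader might infer that the major study will be wrongly sized. The article says only that pilot data will inform its size. Nothing says it would use an untreated control, and with a lecture control the pilot difference is the appropriate input.
- **Referral practices.** The listed content of the control session does not include referral, so dilution of that contrast is not shown.

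None of this reconciles the label with the Methods.

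**Conclusion.** The contradiction is real and can be settled from the text alone: the Discussion attributes to the design a property that the Methods rule out. The knowledge contrast is training beyond a single lecture with demonstration, and the change in controls is not a pure measure of background change. The gap between this contrast and the effect against no education equals the lecture's gain, which the documents do not quantify. The decomposition assumes background change is equal in the two groups, and the power figures are illustrative only.

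It would go too far to say that the trial's conclusions will be mis-stated. They could be, if the no-treatment label is carried into the report. An active comparator is a legitimate choice, and nothing here calls for changing it. The point deserves correction because the comparator determines what the trial can conclude.

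**What to change.** 1. In the Discussion, replace the no-treatment label with wording that matches the Methods, such as *a nonequivalent control group given a single conventional session of oral health teaching*. Keep the argument from a concurrent control and baseline similarity.
2. Name that comparator in the null and alternate hypotheses and in the abstract.
3. Add a statement on interpretation: the between-group knowledge difference is the added effect of the five-day training over that session; the change in controls is not a pure estimate of background change; and the effect against no education is not estimated.

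The cost is wording only. Procedures, sample size and analyses stay as they are, and the claim becomes narrower.

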## Conclusion

The OpenWHO online course on oral health for CHWs in WHO African Region is the first of its kind, with several modules aimed at building participant’s capacity “*on oral health promotion, oral disease prevention, and control to meet some of the unmet demand for oral health services and strengthen the oral health system through a cross-cutting approach*” (61). To the best of our knowledge, no study has been done to document the experiences of trainees and participants engaging in this course. Additionally, this training includes an extra module which will provide culturally appropriate information for maternal and child oral health in this population. Lessons learnt could be useful to strengthen adoption and implementation practices in Nigeria and across the WHO African Region.

## Ethics statement

The studies involving humans have been approved by the Institutional Review Boards at the University of Iowa (IRB-01/202312517); the University of Ibadan/University College Hospital, Ibadan (UI/EC/23/0724); the University of Lagos/Lagos University Teaching Hospital, Lagos (ADM/DSCST/HREC/APP/6454) and Bayero University Kano/Aminu Kano Teaching Hospital, Kano (NHREC/28/01/2020/AKTH/EC/3739), Nigeria. The studies were conducted in accordance with the local legislation and institutional requirements. The participants provided their written informed consent to participate in the pilot study. Written informed consent to participate in the main study will be obtained from participants.
